## Abstract

**Background:**

Physical exercise training aims at reducing disease-specific impairments and improving quality of life in patients with chronic obstructive pulmonary disease (COPD). COPD exacerbations in particular negatively impact COPD progression. Physical therapy intervention seems indicated to influence exacerbations and their consequences. However, information on the effect of physical therapy on exacerbation occurrence is scarce. This study aims to investigate the potential of a protocol-directed physical therapy programme as a means to prevent or postpone exacerbations, to shorten the duration or to decrease the severity of exacerbations in patients with COPD who have recently experienced an exacerbation. Besides, this study focuses on the effect of protocol-directed physical therapy on health status and quality of life and on cost-effectiveness and cost-utility in patients with COPD who have recently experienced an exacerbation.

**Methods/Design:**

A prospective cohort of 300 COPD patients in all GOLD stages will be constructed. Patients will receive usual multidisciplinary COPD care including guideline-directed physical therapy. Patients in this cohort who have GOLD stage 2 to 4 (post-bronchodilator FEV_1_/FVC < 0.7 and FEV_1_ < 80% of predicted), who receive reimbursement by health insurance companies for physical therapy (post-bronchodilator Tiffeneau-index < 0.6) and who experience a COPD exacerbation will be asked within 56 days to participate in a cohort-nested prospective randomised controlled trial (RCT). In this RCT, the intervention group will receive a strict physical therapy programme for patients with COPD. This protocol-directed physical therapy (pdPT) will be compared to a control group that will receive sham-treatment, meaning no or very low-intensity exercise training (ST). An economic evaluation will be embedded in the RCT. Anthropometric measurements, comorbidities, smoking, functional exercise capacity, peripheral muscle strength, physical activity level, health related quality of life, patients’ perceived benefit, physical therapy compliance, motivation level, level of effective mucus clearance, exacerbation symptoms and health care contacts due to COPD will be recorded. Follow-up measurements are scheduled at 3 and 6 weeks, 3, 6, 12 and 24 months after inclusion.

**Discussion:**

Ways to minimise potential problems regarding the execution of this study will be discussed.

**Trial registration:**

The Netherlands National Trial Register NTR1972.

## Background

Chronic obstructive pulmonary disease (COPD) is currently defined as “a common preventable and treatable disease, characterised by persistent airflow limitation that is usually progressive and associated with an enhanced chronic inflammatory response in the airways and the lung to noxious particles or gasses. Exacerbations and comorbidities contribute to the overall severity in individual patients” [1]. The World Health Organisation (WHO) lists COPD as the tenth most prevalent disease worldwide and the fourth most common cause of death in the world, responsible for 5% of overall mortality [2]. Due to the ageing population, expanding smoking behaviour, earlier diagnosis of COPD and reduced mortality from other common causes of death, the total number of people with COPD will increase in the near future. This will rank COPD fifth worldwide in burden of disease by 2020 [1].

Common clinical pulmonary manifestations that can be seen in COPD patients are dyspnoea with chronic cough, sputum production and recurrent respiratory infections. Additionally, with disease progression significant extrapulmonary systemic effects can be observed in patients, especially in patients with moderate to severe airway obstruction: skeletal muscle dysfunction and weakness, nutritional abnormalities and weight loss [1,3]. Nowadays, systemic effects of COPD are acknowledged as an important characteristic of the disease, which contribute significantly to decreased exercise capacity, decreased health status, reduced health related quality of life (HRQL), more utilisation of health care resources and increased mortality [3-5].

### The impact of COPD exacerbations

The definition of COPD by the Global Initiative for Chronic Obstructive Lung Disease (GOLD) explicitly mentions COPD exacerbations as an enormous burden for patients [1] and health care systems [6]. Exacerbations are defined as “an event in the natural course of the disease characterised by an increase in dyspnoea, cough and/or sputum beyond normal day-to-day variations. The onset is seemingly acute and may require a change in regular medication or hospitalisation” [1,7]. They are mostly precipitated by an infectious systemic inflammation of the upper respiratory tract and the tracheobronchial tree [1].

Since exacerbations are a significant cause of morbidity (e.g. acute muscle deconditioning and muscle weakness), hospital admissions, impaired health status, impaired quality of life and even death in patients [8-10], prevention is indicated. A relatively small percentage of patients (10%) experiencing frequent exacerbations account for over 70% of all medical costs due to COPD [6]. A study of Pitta et al. (2006) showed that COPD patients tend to be severely inactive during and after an exacerbation; which is worrying since there seems to be a strong association between physical inactivity in patients who recently exacerbated and an elevated risk of (re)hospitalisation due to a COPD exacerbation [11,12]. It appears that patients with recurrent exacerbations show a more rapid decline in their physical activity level than stable patients and their functional capacity gradually decreases faster over time [11]. Besides, their more pronounced skeletal muscle weakness and decreased six-minute walk distance (6MWD, a measure of functional exercise capacity), are risk factors for future exacerbations and higher mortality [9,13]. Consequently, unstable patients, who frequently experience exacerbations, enter a downward spiral of inactivity and exacerbations. Hence, adequate management of exacerbation (prevention) in patients is considered worldwide as one of the main goals in controlling COPD [1].

Although medical treatment modalities for COPD have improved, there is still no pharmacological therapy available that reduces the progression of the disease [4]. Though, patients with COPD, irrespective of disease stage, have shown to benefit from exercise programmes [12] resulting in improved exercise performance and health status [4,5,14-17].

### Physical exercise training in COPD

Evidence, to support the biological plausibility of the positive effects of physical exercise training on COPD, points towards longer high-intensity exercise training programmes. High-intensity exercise training has shown to increase exercise tolerance [18,19]. Firstly, exercise training improves muscle oxidative capacity and oxygen recovery kinetics in patients with COPD [20]. Secondly, patients with COPD who experience lactic acidosis during exercise can attain physiologic training responses from a physical exercise training programme [21,22]. Exercise performance can be improved by reducing the ventilatory requirement for a certain activity level. As the bioenergetics of skeletal muscle improve, blood lactate levels are reduced at a given level of exercise; thereby decreasing the amount of non-metabolic carbon dioxide (CO_2_) that is produced by the bicarbonate buffering system [12,21]. Since lactic acid stimulates ventilation, decreasing lactate production during exercise can be very helpful for patients with COPD. Physical exercise training, in addition to optimal bronchodilatation, can reduce breathing frequency during exercise and consequently lower the degree of dynamic lung hyperinflation that many patients with severe COPD develop [22,23]. In turn, decreased hyperinflation may mediate improvement in exercise endurance by delaying the attainment of a critically high inspiratory lung volume [22,23]. Moreover, high-intensity exercise training, engendering high levels of blood lactate, are more effective than training work rates eliciting low lactate levels [21]. Although measurable physiological changes may occur within weeks, behavioural changes may require longer time periods and may be the reason that greater effects were shown in long-term exercise programmes [19]. In conclusion, extensive physical exercise training is beneficial in patients with COPD.

### Physical exercise training to reduce COPD exacerbation frequency, duration or severity

Patients with COPD often experience sudden worsening of symptoms, i.e. exacerbations. Previous studies already demonstrated that physical exercise training (the component that has shown to provide the most benefit of pulmonary rehabilitation programmes) [1] has important benefits for patients, such as improved exercise capacity and HRQL [9,15,24]. However, the effect of pulmonary rehabilitation and physical exercise training on the occurrence of exacerbations is less clear [4,19,25,26]. Observational studies demonstrated that patients who perform regular physical activity have a reduced risk of hospital admission due to COPD and decreased all-cause and respiratory mortality [12,27,28], but neither of these outcomes are a substitute for reduction of exacerbation frequency, duration or severity. The factors determining utilisation of health care resources in patients with COPD are poorly understood [29]. Few studies reported significantly fewer exacerbations after a pulmonary rehabilitation program (including physical exercise training) [30,31]. Reduction of exacerbations may be at least one of the factors explaining the reduction in health care utilisations as reported in observational studies. Moreover, a recent study suggested that an acute bout of exercise resulted in a reduction in sputum proinflammatory cytokines, suggesting some anti-inflammatory effect of exercise in the airways of patients with COPD [32]. Based on these few findings it is plausible to hypothesise that physical exercise training for patients with COPD may result in fewer exacerbations, or at least in less severe exacerbations, meaning exacerbations with a shorter duration or exacerbations without the necessity for hospital admission.

Prevention of exacerbations by means of physical exercise training would fit the prime management goal for COPD [27]. Based on expert’s opinion, it was stated that teaching patients how to recover quickly from an exacerbation will probably minimise the risk for relapse and improve long-term outcome [26]. Exercise training improves recovery in patients with COPD after an acute exacerbation [33]. Also, from previous studies it has been shown that especially *early* pulmonary rehabilitation (including physical therapy) after an acute exacerbation is most likely to result in clinically relevant improvements in functional exercise capacity and health-related quality of life [5,16]. Puhan et al. (2011) found in nine small trials of moderate methodological quality that effects of pulmonary rehabilitation programmes immediately after an acute COPD exacerbation were visible when at least physical exercise was included [24]. However, they also concluded that more studies are needed to further investigate the role of pulmonary rehabilitation after an acute exacerbation and its potential to reduce costs [24,34].

Evidence based physical exercise training and advice on physical activity can be delivered by physical therapists that follow evidence based guidelines for physical therapy in COPD patients, such as the guideline COPD developed by the Royal Dutch Society for Physical Therapy (KNGF) [35]. This study protocol hypothesis that early protocol-directed physical therapy for patients with COPD may reduce COPD exacerbation frequency, duration or severity.

## Methods/Design

### Study aim

The aim of this study is to assess the clinical effectiveness, cost-effectiveness and cost-utility of early protocol-directed physical therapy for patients with COPD on exacerbations (frequency, duration and severity), health status and quality of life in patients who have recently experienced a COPD exacerbation.

### Study design

A cohort-nested, prospective, randomised controlled trial (cohort-nested RCT) will be conducted. This means that a RCT will be embedded within a COPD cohort (Figure 1). The cohort will consist of COPD patients who receive usual multidisciplinary COPD care and guideline-directed physical therapy (gdPT). The cohort will serve as an optimal recruitment population for the RCT to show the surpassing importance of physical therapy interventions on exacerbations. Therefore, a RCT that holds a large contrast of protocol-directed physical therapy (pdPT) versus sham treatment (ST) will be constructed. This means that when patients from the COPD cohort report an exacerbation, with an occurrence no longer than 56 days ago (a trade-off between threshold values of 35–91 days in which the majority of exacerbations have returned to baseline [36]), they are either randomised to the experimental group (protocol-directed physical therapy (pdPT)) or the control group (sham-treatment (ST)). This RCT will be used to study effectiveness of physical therapy in addition to an economic evaluation.

**Figure 1 F1:**
[figure not shown]
**Framework of the study: a cohort-nested, prospective, randomised controlled trial.** Definition of abbreviations: COPD = Chronic Obstructive Pulmonary Disease; RCT = Randomised Controlled Trial; Tiffeneau < 0.6 = Tiffeneau index (FEV_1_/VC) < 0.6*; FEV_1_ = Forced Expiratory Volume in one second*; FVC = Forced Vital Capacity*; GOLD I = mild COPD, FEV_1_/FVC < 0.7 and FEV_1_ ≥ 80% of predicted*; GOLD II = moderate COPD, FEV_1_/FVC < 0.7 and 50% ≤ FEV_1_ < 80% of predicted*; GOLD III = severe COPD, FEV_1_/FVC < 0.7 and 30% ≤ FEV_1_ < 50% of predicted*; GOLD IV = very severe COPD, FEV_1_/FVC < 0.7 and FEV_1_ < 30% of predicted *or* FEV_1_ < 50% of predicted* plus chronic respiratory failure. *All lung functions are post-bronchodilator values.

The ethics committee of Maastricht University has approved the study protocol, procedures and informed consent (NL28718.068.09).

### Study population

The study population consists of patients who are treated by COPD-specialised physical therapists, after referral by a general practitioner (GP) or pulmonologist. Physical therapy practices, GPs and pulmonologists, in southern districts of the Netherlands, who are willing to participate in the study, will be recruited. Once a patient is referred to a participating physical therapy practice (with post-bronchodilator FEV_1_/FVC < 0.7, GOLD 1–4), the patient will be asked to participate in the COPD cohort study. Patients in the cohort are monitored for health outcomes and exacerbation occurrence. Participants for the RCT will be recruited within the cohort by physical therapists, as soon a patient suffers from an exacerbation. Additionally, advertisements in local papers in southern regions of the Netherlands are used to reach potential COPD patients for the RCT who were missed out on inclusion with the former recruitment method. Those patients who are reached through advertising and presenting with an exacerbation will be recruited for the RCT by the researcher, while the mechanisms for alert and continuous trial recruitment are automatically organized within the cohort. By means of this unique cohort-nested RCT design (Figure 1), the likelihood that patients with a COPD exacerbation will be picked up is higher. A flowchart of the RCT is presented in Figure 2.

**Figure 2 F2:**
[figure not shown]
**Flowchart of the RCT.** Definition of abbreviations: COPD = chronic obstructive pulmonary disease; pdPT = protocol-directed physical therapy; ST = sham-treatment, including no or very low-intensity exercise training.

The following inclusion criteria will be checked during the eligibility screening of patients for the RCT: a GP/pulmonologist diagnosed COPD in GOLD stage 2, 3 or 4 (supported by a post-bronchodilator FEV_1_/FVC < 0.7 and FEV_1_ < 80% of predicted); eligible for reimbursement by health insurance companies for physical therapy (post-bronchodilator Tiffeneau-index < 0.6); experienced an COPD exacerbations in the past 56 days (defined as: unscheduled visit to their GP/pulmonologist or hospitalisation and possibly receiving a course of antibiotics and/or prednisone); having an adequate and optimal medication (inhalation) regimen by their referring physician; willing to sign informed consent before randomisation; competent enough to speak and understand the Dutch language; above 18 years of age.

Patients who meet the following criteria will be excluded from the RCT: suffering from significant exercise limitations or comorbidities that would prevent a patient from following the required intervention in this study; and expected to be lost for follow-up (for example because of a planned change of residency).

All patients entering the cohort have to give informed consent on the following two levels, whereas patients entering the RCT have to give informed consent on three levels: (1) oral consent to exchange patient information between physical therapists and other related health care providers (usual physical therapy procedure); (2) oral consent to participation in the COPD cohort (registration and use of data for research purposes); and (3) written consent to participate in the RCT, after experiencing an acute exacerbation.

### Size of the study population

For the cohort study 300 patients with COPD will be recruited. This number is based on the calculated sample size for the RCT part of the study. The sample size calculation for this RCT is based on the identification of a minimal relevant clinical difference in exacerbation frequency between the experimental and the control group. The difference in exacerbation rate is expected to be 22% (based on exacerbation rates found in previous studies with rehabilitation programmes) [37,38]. The probability that the study will detect a treatment difference is 80% at a two-sided 5% significance level. This is based on the assumption that the intervention period will be 12 months, the follow-up period will be 24 months and the ratio control subjects to intervention subjects is 1:1. A sample size calculation for comparing event rates between two independent groups is used, resulting in 79 participants per group [39,40]. Assuming outcome data will be analysed prospectively and considering a drop-out rate of 20%, 100 patients per group will be needed in this two treatment parallel-design study.

### Randomisation and blinding

After taking baseline measurements and eligibility screening within 56 days after the start of the past exacerbation, informed consent is obtained and stratified block randomisation will take place (Figure 2). Pre-stratification will be applied for exacerbation severity and GOLD stage (six levels in total), since both factors are suspected to influence treatment outcome. Therewith, the influence of selection bias for severity of the disease on group configuration or comparability between groups may be minimized. The patients will be randomly assigned to the experimental group or the control group in a 1:1 ratio. The concealed randomisation procedure will be performed by a blinded, independent research assistant using a computerised system. A block-randomisation will be used with blocks of size four, six or eight, with random block sequences. A computerized system will refer the patients to a group, after which a blinded, independent research assistant will notify the treating physical therapist after receiving instructions on treatment group allocation through computer generated random number tables.

In this RCT full blinding of the patients and physical therapists is not feasible. However, Hawthorne effects are non-differential, since patients in the experimental group as well as patients in the control group will get attention from their physical therapist. Both groups receive periodic questionnaires and measurement sessions, avoiding non-random effect optimisation. Several measures are taken to avoid bias due to blinding issues. Although patients will be aware of the existence of two treatment arms, they are not informed about the exact content of the other treatment arm (e.g. determining intensity) to prevent influence on outcomes. The control group will be assessed at the same time intervals as the experimental group by trained physical therapists that do not assess the patients in the experimental group at the same time. The researcher is fully blinded, because all outcome measures are quantified by the patients and physical therapists. Physical therapists are blinded for a number of outcomes measurements (questionnaires CCQ, CRQ-SR, GPE, EQ-5D, DS14 and physical activity level), since part of the data that are provided by the patient alone and will be captured through an electronic patient record system. Moreover, a number of important objective outcomes (exacerbation frequency, duration and severity, mechanically assessed physical activity level and cost diaries) are less liable to patient manipulation in order to please their physical therapist, as these outcomes are directly collected by the researcher.

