	** *Intervention* **	** *Content* **	** *Intensity* **	** *Frequency* **	** *Start* **
Cohort	**Guideline-directed physical therapy (gdPT):**	One or more of:	Ranging on the full intensity scale	On average:	
		Exercise training, peripheral muscle strength training, respiratory muscle training, breathing exercises, electrical muscle stimulation, physical activity in daily life (homework)		30 minutes to 1 hour	
	A programme made by individual PTs, within the limitations of the KNFG physical therapy guideline for COPD (usual care)				
				1 to 3 times a week	
				During 3 months to multiple years	
RCT experimental group	**Protocol-directed physical therapy (pdPT):**	Both exercise training and peripheral muscle strength training;	Endurance/ interval training ≥ 60% of (sub) maximum, muscle strength training ≥ 80% of maximum, always: borg-scale ≥5	Minimal:	*Early* PT: starting within 56 days after an acute exacerbation
				1 hour	
	A complete programme by protocol, according to the KNGF physical therapy guideline for COPD, but with strict conditions			Twice a week	
		When indicated: respiratory muscle training, breathing exercises, electrical muscle stimulation		During 12 months	
		Always: physical activity in daily life (homework)			
RCT control group	**Sham-treatment (ST):**	One-time consultation: advice to be physically active in daily life			
	No physical therapy				
	*Or*				
				Maximal:	
	Very low-intensity exercise training	Exercise training only	Endurance/ interval training ≤ 15% of (sub) maximum or borg-scale ≤2	30 minutes	
				Once a week	
				During 12 months	

Definition of abbreviations: RCT = randomised controlled trail; COPD = chronic obstructive pulmonary disease; KNGF = the Dutch Society for Physical Therapy.

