#### *Experimental group*

Patients in the experimental group receive protocol-directed physical therapy (pdPT). The content of the pdPT is based on the on the KNGF physical therapy guidelines for COPD, like the guideline-directed physical therapy in the cohort [35]. However, in the RCT the physical therapy follows a strict protocol. The therapy specifically concerns *early* physical therapy, starting within 56 days after an acute COPD exacerbation. Patients in the experimental group receive a programme of one hour, twice a week for one year. The programme includes high-intensity exercise training, which entails endurance and/or interval training with an intensity of 60% or higher of (sub) maximum physical exertion, based on the results of a maximal cardiopulmonary exercise test (CPET) and six-minute walk test. In addition, ratings of perceived exertion and dyspnoea of five or higher on the modified Borg-scale (0–10) are used to tailor exercise intensity [42]. Peripheral muscle strength training is provided (a programme combining upper and lower extremities) with an intensity of 80% or higher of maximum physical exertion, based on the results of one-repetition maximum tests or handheld dynamometer measurements. Again, ratings of perceived exertion and dyspnoea of five or higher on the modified Borg-scale are used to adjust exercise intensity [9]. When indicated, the programme includes respiratory muscle training, breathing exercises and electrical muscle stimulation. In addition, much emphasis is given to the assessment and treatment of physical inactivity in daily life. Patients are asked to increase their total physical activity on their own. At least 30 minutes of moderately intense physical activity on at least five days a week is the current recommended level. All visits for treatment and all advice for home training are part of standard procedure, following the KNGF guideline physical therapy for COPD and the Dutch Standard for Healthy Exercise (NNGB) [35,43]. An additional file shows the intervention in more detail according to a framework based on the International Classification of Functioning, Disability and Health (ICF) [see Additional file 1] [44].

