#### *Control group*

Patients in the control group receive sham-treatment (ST), which entails no or very low-intensity exercise training, for one year. The latter applies only if the participant in the control group insists on training in a physical therapy practice. The very low-intensity exercise training is limited to a maximum of 30 minutes once a week, with an intensity of 15% or lower of (sub) maximum physical exertion, based on the results of a maximal CPET and six-minute walk test. In addition, ratings of perceived exertion and dyspnoea of two or lower on the modified Borg-scale (0–10) are used to tailor exercise intensity [42]. There will be no further peripheral muscle strength training, respiratory muscle training, breathing exercises nor electrical muscle stimulation [35]. Furthermore, patients will be advised to do at least 30 minutes moderately intense physical activity on their own for at least five days a week according to the physical activity norm [43].

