#### *Planning of outcome assessment*

In all eligible patients, entering the cohort and the RCT, baseline assessment will be performed. In the baseline assessment, demographic variables, anthropometric data, healthcare/medical variables, lifestyle factors, health related quality of life and clinical status will be recorded of the participants.

The lung function of the patients is already assessed by the GP/pulmonologist or assistant, by means of pulmonary function tests, as part of standard procedure in patients with COPD. Forced expiratory volume in one second (FEV_1_ (L)), forced vital capacity (FVC (L), the FEV_1_/FVC ratio and Tiffeneau-index (FEV_1_/VC) are measured by means of post-bronchodilator spirometry and are known to the physical therapist in order to construct a tailored-made programme adjusted to the severity of the pulmonary component of the disease. The clinical status, maximal exercise capacity and physiological restrictions of the patients should in most cases have been assessed by a maximal CPET and communicated to the physical therapist in order to enable the physical therapist to construct a safe and tailored-made programme for the patient. If the clinical status of the patient in the RCT is not yet assessed in the hospital or rehabilitation clinic, the treating physical therapist will be asked to refer the patient for a maximal CPET to a sports medicine physician, who is contacted by the researcher.

After the baseline visit, participants in the cohort will be assessed every three months for 12 months or longer. Participants from both the experimental and the control group in the RCT will be measured at three and six weeks, and three, six, twelve and twenty-four months during follow-up visits at the physical therapy practice for various outcome measures (Figure 3).

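### The protocol says therapist attention is balanced between the arms, but its own schedule gives controls at most half the treatment sessions and a quarter of the hours

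*Protocol article*

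**What the plan says.** The section Randomisation and blinding concedes that patients and therapists cannot be fully blinded. It then offers this reassurance: "Hawthorne effects are non-differential, since patients in the experimental group as well as patients in the control group will get attention" from their physical therapist. The next sentence adds that both arms have the same questionnaires and measurement sessions.

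The treatment content is set out elsewhere:

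- **Experimental arm** (Experimental group; Table 1): patients "receive a programme of one hour, twice a week for one year". Table 1 marks this frequency as a minimum.
- **Control arm, default** (Table 1): no physical therapy, with the content given as "One-time consultation: advice to be physically active in daily life".
- **Control arm, alternative** (Control group): very low-intensity training, "limited to a maximum of 30 minutes once a week". On when it is given: "The latter applies only if the participant in the control group insists on training in a physical therapy practice".
- **Both arms** (Planning of outcome assessment): patients are "measured at three and six weeks, and three, six, twelve and twenty-four months during follow-up visits at the physical therapy practice".

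Two other sections bear on the point. Bias and confounding speaks only of minimising differential Hawthorne effects through standardised monitoring. Potential problems acknowledges that control patients are treated less often.

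**The concern.** The reassurance is stated as a fact about the design, and it comes first among the answers to the lack of full blinding. The reason given is attention from the physical therapist. That holds only if the arms receive comparable attention, and the schedule shows that they do not. Calling the comparator a sham strengthens the impression, because a sham is normally understood to reproduce the contact that goes with a treatment.

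Several outcomes could respond to contact, encouragement and expectation as well as to training. The CCQ, CRQ-SR, EQ-5D and Global Perceived Effect (GPE) are completed by the patient. Symptom-based exacerbations are rated by the patient on diary cards. The CCQ and CRQ-SR are also the effect measures in the cost-effectiveness analysis, and the EQ-5D supplies the QALYs. A reader who accepts the reassurance would think attention had been ruled out as a contributor to differences in these outcomes.

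**Working it through.** The protocol gives no total for contact, so there is no stated figure to reproduce. The totals below follow from the prescribed frequency and session length over the 12-month treatment period.

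**Treatment contact per patient**

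Sessions = sessions per week × 52. Hours = sessions × hours per session.

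| Arm | Sessions | Hours |
|---|---|---|
| pdPT (prescribed minimum) | 2 × 52 = 104 | 104 × 1 = 104 |
| Control, default | 1 consultation | length not stated |
| Control, on insistence (maximum) | 1 × 52 = 52 | 52 × 0.5 = 26 |

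Maximum control against pdPT: 52/104 = one half of the sessions; 26/104 = one quarter of the hours.

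**Adding the measurement visits**

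Within the treatment year, both arms have a baseline visit and five follow-ups (weeks 3 and 6, months 3, 6 and 12), so six visits. Their length is not stated. Assume 0.5 to 2 hours per visit, and 1 hour for the single consultation.

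- At 0.5 h per visit (6 × 0.5 = 3 h): pdPT 104 + 3 = 107 h; default control 1 + 3 = 4 h; maximum control 26 + 3 = 29 h. The ratios are 107/4 ≈ 27 and 107/29 ≈ 3.7.
- At 2 h per visit (6 × 2 = 12 h): pdPT 104 + 12 = 116 h; default control 1 + 12 = 13 h; maximum control 26 + 12 = 38 h. The ratios are 116/13 ≈ 9 and 116/38 ≈ 3.1.

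Counting every shared visit as therapist attention therefore reduces the imbalance but does not remove it.

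**The arm as a whole**

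Let q be the share of controls who insist and then train at the maximum, and count one contact for each of the others. Mean control treatment contacts are (1 − q) × 1 + q × 52. This gives 1 at q = 0, 26.5 at q = 0.5 and 52 at q = 1, against 104 for pdPT. The protocol gives no value for q, so no single ratio for the arm can be stated. No value of q brings the arms level.

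**The case against.** Five points can be made for the protocol.

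1. **Measurement is balanced.** Effects of being observed and assessed are scheduled equally, and in that narrow sense the claim is defensible. This stands. But the protocol's stated reason is therapist attention, and equal visits do not make a year of twice-weekly sessions equal to one consultation.
2. **The protocol is more careful elsewhere.** Bias and confounding treats differential Hawthorne effects as something to be minimised. This also stands. It confines the error to one over-strong statement, and it shows that the two sections do not agree.
3. **The large contrast is deliberate and disclosed.** Study design says so, Table 1 sets it out, and the sham label is spelled out as no or very low-intensity training. The comparison is legitimate, and nothing here calls for another control arm. It simply cannot also be described as balanced for attention.
4. **There are blinding safeguards.** Patients are not told the exact content of the other arm, and therapists do not see the questionnaire answers. These may reduce bias in reporting, but they do not equalise contact.
5. **The target is already the programme.** Study aim and the Clinical effectiveness analysis concern physical therapy as delivered, of which therapist contact is a part. This is correct and bears on the first reading below.

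Three stronger readings are tempting, and the documents do not support them.

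- A reader might infer that the protocol will present differences as effects of exercise intensity free of attention. No section says this.
- A reader might quote 104 to 1 as the ratio of therapist contact. That figure compares treatment sessions with the default control only. It leaves out the measurement visits and the controls who train.
- A reader might conclude that the event-based exacerbation count is biased. That definition needs an unscheduled contact with extra medication, or a hospital or emergency visit, and both arms keep daily diaries. Therapists do also look for events through missed appointments, so detection could differ by arm, but the document does not allow a direction or size to be given.

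**Conclusion.** The statement is wrong as written. The trial balances scheduled measurement; it does not balance therapist attention. Under the most generous control option the protocol allows, controls have half the treatment sessions and a quarter of the treatment hours of pdPT. Under the default they have one consultation.

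The figures are prescribed contact, not attended contact. They rest on 52 weeks of treatment at the stated frequencies. The ratios that include measurement visits also rest on assumed visit and consultation lengths.

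The consequence is one of interpretation. Differences in the CCQ, CRQ-SR, EQ-5D, GPE and symptom-based exacerbations can be read as effects of the whole pdPT programme, contact included. The design does not support a claim that attention has been controlled. The randomised comparison, the sample size and the choice of comparator are not put in question by this point.

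**What to change.** - In Randomisation and blinding, withdraw the statement that attention effects are equal. Say instead that measurement contact is scheduled equally and that therapist contact differs by arm. This brings the section into line with Bias and confounding.
- Describe the comparator as no physical therapy, or very low-intensity training on request, and not as a sham that controls for attention.
- State that differences in the CCQ, CRQ-SR, EQ-5D, GPE and symptom-based exacerbations reflect the whole pdPT programme, including therapist contact.
- Report therapist contacts per arm, using the session counts and durations that Data collection says the record system holds. Include the number of controls who chose training, so that the actual contrast can be seen.

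The cost is some rewording and one descriptive table from data already collected. Treatment, sample size and data collection are unchanged. The downside is a less favourable claim about control of bias.
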